## Abstract

**Background:**

Out-of-hospital cardiac arrest (OHCA) is a leading cause of preventable mortality that now affects almost 3,000 people each year in Ireland. Survival is low at 6–7%, compared to a European average of 8%. The Irish Out-of-Hospital Cardiac Registry (OHCAR) prospectively gathers data on all OHCA in Ireland where emergency medical services attempted resuscitation.

The Irish health system has undergone several developments that are relevant to OHCA care in the period 2012–2020. OHCAR data provides a means of exploring temporal trends in OHCA incidence, care, and outcomes over time. It also provides a means of exploring whether system developments were associated with a change in key outcomes.

This research aims to summarise key trends in available OHCAR data from the period 2012 – 2020, to explore and model predictors of bystander CPR, bystander defibrillation, and survival, and to explore the hypothesis that significant system level temporal developments were associated with improvements in these outcomes.

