## Introduction

### Out-of-Hospital Cardiac Arrest

Out-of-hospital cardiac arrest (OHCA) describes the sudden loss of mechanical function of the heart and the absence of blood flow around the body, occurring outside of a hospital setting
^
1,
2
^. OHCA is the most time-critical medical emergency, with survival depending on the prompt actions of the community where OHCA occurs, emergency medical services (EMS) and in turn, appropriate follow-on hospital care
^
3
^. Internationally, the annual incidence of OHCA treated by emergency medical services (EMS) is estimated to be 30 – 97 individuals per 100,000 population, median age ranges from 64 to 79 years and more than half of victims are male
^
4
^. OHCA with attempted resuscitation has an incidence of 56 per 100,000 population per year in Europe and is considered the third leading cause of death
^
5
^. Survival to/ immediately after hospital discharge ranges from three to twenty percent internationally and is eight percent in Europe
^
6
^. Of those that do survive to discharge in Europe and North America, approximately seventy percent are still alive at three years
^
7
^. In Ireland there are now almost 3,000 OHCAs with attempted resuscitation each year of which six to seven percent involve survival to hospital discharge
^
8
^.

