### Focus of this study

This study will examine data from the Irish Out-of-Hospital Cardiac Arrest Registry (OHCAR) to describe OHCA incidence and its care processes in Ireland over the period 2012 to 2020. We will further interrogate this data to identify key OHCAR variables that predict key outcomes. We anticipate approximately 18,000 relevant observations will be available for analysis. We will consider survival to hospital discharge, bystander CPR, and bystander defibrillation to be key outcomes of interest over the study period. We hypothesise that of the timeline of OHCA developments described above, two key developments are likely to be associated with a significant change in outcomes. Given the scale of reorganisation and centralisation of EMS control in 2015 and 2016 on the backdrop of the ongoing NAS ‘one life’ project we hypothesise that the NAS transition from a system of multiple regional independent control centres to the single national control centre (NEOC) would be associated with improvements in bystander CPR and survival to hospital discharge. In turn, given Covid-19’s detrimental effect on OHCA internationally we hypothesise that COVID-19 would be associated with significant reductions in bystander CPR, bystander defibrillation and survival to hospital discharge in Ireland.

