### Study population, setting and time frame

The population for this study will be patients of all ages who suffered un-witnessed, or bystander witnessed OHCA during the time period 2012 – 2020 and are included in the Irish national OHCAR cardiac arrest registry database. Patients who had an EMS witnessed OHCA will be specifically excluded from this current study. Follow on work will consider this distinct excluded group separately.

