		**Not Covid Period**				

### Statistical model building and interpretation procedures

For each outcome we will build a logistic model: initially a full model with all relevant predictors will be fitted. A refined model will then be built using a stepwise model selection procedure (STEPAIC function in R). This procedure builds several models from all possible combinations of the predictors by sequentially adding and dropping predictors and finally selects the model with the lowest AIC. The stepwise model will then be further improved by examining addition of pairwise interaction variables and retaining any interactions which improve fit. We will evaluate each model (full, stepwise and with interactions) based on AIC. In addition, the model deviance and a Hosmer-Lemeshow Goodness of Fit (GOF) test will be inspected for each model. To assess linearity between continuous predictors and the log odds of the outcome we will rely on good model fit as indicated by the Hosmer-Lemeshow goodness of fit test. We will also use logistic regression with higher order terms (polynomial terms) to explore if the relationship between the outcome and the continuous predictors is indeed non-linear. If higher-order terms are significant, these will be retained in the model, otherwise they will be dropped from the model. We will also attempt to ameliorate fit by including pair-wise interaction terms between predictors. We will summarise the effect of each individual variable in the final model using odds ratios and 95% confidence intervals. The effect of any significant interactions in the final model will be explored graphically. After selecting the final model from the three models, we will evaluate the predictive ability of the final best fitting model using 10-fold cross-validation and evaluate the prediction accuracy for the model.

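### Cross-validation starts only after the model has been chosen on all the data, so predictive ability is modestly overstated; for survival at 6–7%, raw accuracy would also say little

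*Protocol article*

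**What the plan says.** The relevant text is in the Methods, under Statistical model building and interpretation procedures. The same sequence applies to all three outcomes: "For each outcome we will build a logistic model: initially a full model with all relevant predictors will be fitted". Stepwise selection by AIC follows. Next, "The stepwise model will then be further improved by examining addition of pairwise interaction variables", and those that improve fit are kept. Polynomial terms stay if they are significant. The full, stepwise and interaction models are compared on AIC, with deviance and a Hosmer-Lemeshow test also inspected.

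Validation is placed after the choice among the three models has been made: "we will evaluate the predictive ability of the final best fitting model using 10-fold cross-validation and evaluate the prediction accuracy for the model". No definition of accuracy, no cut-off and no discrimination measure is given.

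On size, the section Focus of this study states: "We anticipate approximately 18,000 relevant observations will be available for analysis". The Introduction says of resuscitation attempts in Ireland, "each year of which six to seven percent involve survival to hospital discharge", and the Abstract gives the same range. The study population is narrower than the one behind that rate: "Patients who had an EMS witnessed OHCA will be specifically excluded from this current study".

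**The concern.** Cross-validation gives an honest estimate only if the held-out records played no part in building the model. Here all records are used to decide which main effects, curves and interactions appear. Refitting only the coefficients within folds leaves that selection untested, so chance patterns that earned a term its place are still present in the fold meant to test it.

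The second matter is the measure. For a rare outcome, the proportion correctly classified is dominated by the common class. A model with no predictors scores almost as well as a good one.

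At stake is how far readers can trust the stated predictive ability of the three models. Modelling predictors is one of the four study aims, and the Discussion intends the results to inform system design.

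**Working it through.** The article states no accuracy, AUC or sample-size calculation, so there is no figure of its own to reproduce.

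**Inputs.** About 18,000 records (Focus of this study); survival 6–7% (Abstract and Introduction); 22 variables marked for survival and 14 for each bystander outcome (Table 1); order of selection and validation (Statistical model building and interpretation procedures).

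**1. Events.** 18,000 × 0.06 = 1,080 and 18,000 × 0.07 = 1,260 survivors. Per Table 1 variable this is 1,080 / 22 = 49 to 1,260 / 22 = 57. That is ample for main effects, so any optimism comes mainly from the interaction search.

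**2. Spurious interactions.** AIC keeps a null one-degree-of-freedom term when its chi-square exceeds 2, and P(χ²₁ > 2) = 0.157. Interactions are added to the stepwise model, so the number of pairs depends on how many predictors survive. Assume for illustration that 10 of the 22 predictors have real effects:
- predictors kept: 10 + 12 × 0.157 = 11.9
- pairs among them: 11.9 × 10.9 / 2 ≈ 65
- null pairs kept: 65 × 0.157 ≈ 10

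**3. Effect on AUC, stated order.** Simulation settings: n = 18,000, 6.5% events, 22 predictors of which 10 are real, no true interactions, stepwise selection first, then a one-pass AIC threshold for interactions, 6 replicates per signal strength. Between 8 and 9 interactions were kept.

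| Assumed signal | AUC, cross-validated after selection | AUC, selection inside folds | Difference |
|---|---|---|---|
| Weak | 0.665 | 0.652 | 0.013 |
| Moderate | 0.826 | 0.821 | 0.005 |

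A further simulation in the same order kept about 10 null interactions and gave differences of about 0.008 to 0.02. Together the range is roughly 0.005 to 0.02.

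**4. Accuracy of a rule with no predictors.** Predicting death for everyone is correct in 1 − 0.07 = 93% to 1 − 0.06 = 94% of patients.

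**5. What a model adds to that.** This simulation used n = 18,000, 6.5% events, 20 predictors, an assumed cut-off of 0.5 and 4 replicates per setting. It searched all pairs without a stepwise stage, so it is used here only for the behaviour of accuracy. Accuracy and sensitivity are cross-validated after selection.

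| AUC, about | Accuracy, model | Accuracy, death for all | Gain (points) | Sensitivity |
|---|---|---|---|---|
| 0.69 | 93.58% | 93.57% | 0.01 | 0.15% |
| 0.84 | 93.71% | 93.55% | 0.16 | 8% |
| 0.92 | 94.65% | 93.61% | 1.04 | 32% |

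A model with good discrimination (AUC about 0.84) would thus be reported as about 0.2 points better than no model. With selection repeated inside the folds, the accuracies were 93.57%, 93.60% and 94.50%, which is lower by 0.01, 0.11 and 0.15 points. The order of selection and validation therefore barely shows in accuracy; it shows in AUC.

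**The case against.** The strongest reply is that this is a closing check. The aims concern trends, predictors and period effects, reported as odds ratios with confidence intervals, and no prediction tool is to be deployed. Cross-validation changes no estimate. The accuracy phrase may also be meant generically, and the exact measure and cut-off are details that an article can leave to a fuller plan. That limits the weight of the point, and the second part of it is accordingly conditional. It does not remove the first part: the order of selection and validation is stated, and following it as written gives an optimistic result.

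Several stronger readings are tempting, and the documents do not support them.

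- *About 36 spurious interactions in the survival model.* This is 231 pairs × 0.157 and assumes that all 22 variables enter the interaction search. The article adds interactions to the stepwise model. Some pairs are also empty or redundant: the transition and post-transition indicators never coincide, and 2020 lies wholly inside the post-transition period. Some variables have three categories, so their pairs are not single terms. The figure of 14 for the bystander models (91 pairs × 0.157) likewise assumes that nothing is dropped.
- *The final model predicts worse than main effects alone.* This depends on assuming that no interaction is real, which the documents do not say.
- *The reported AUC or calibration slope will be inflated.* The article names neither measure. AUC serves here only to express the size of the bias.
- *Accuracy cannot distinguish the model from predicting death for all.* This is too absolute, since a very strong model gains about 1 point.
- *The rare-event argument covers all three outcomes.* No rates are given for bystander CPR or bystander defibrillation.

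**Conclusion.** The point holds in limited form. Validation after selection on all the data biases the reported predictive ability upward for all three outcomes. For survival, the size is about 0.005 to 0.02 in AUC. That is an order of magnitude from few replicates, and it rests on an assumed signal strength, an assumed 10 real predictors out of 22 and no true interactions. The simulation settings do not include the polynomial search.

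If accuracy means the proportion correctly classified, its floor for survival is about 93–94% and it can hardly show whether the model is useful. The 6–7% covers all resuscitation attempts, while this study leaves out EMS-witnessed arrests, so the floor in the study population may differ somewhat.

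This should be corrected because it is cheap and the stated order is unsound. A reader might infer that the analyses of the transition and COVID-19 periods are compromised by it. They are not, because they rest on odds ratios that this validation step does not touch.

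**What to change.** State that the complete selection sequence (stepwise, polynomial terms, interactions and the choice among the three models) is repeated inside each training fold, with the held-out fold used only for assessment. A bootstrap of the whole sequence would serve equally well.

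Replace raw accuracy by AUC, Brier score compared with the null model, and calibration slope and plot. If a cut-off is used, state it and report sensitivity and specificity.

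The cost is some scripting, computing time and slightly less favourable reported performance. No new data are needed. Choosing the final model by AIC can stay; choosing it on validated performance instead would be a preference, not a correction.

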### Missing data and sensitivity analysis

We anticipate some missing data in both the outcome and predictor variables. We will document the amount of missing data for each variable and graph missing data patterns across the entire dataset. To conduct sensitivity analysis, results from complete case analysis and multiple imputation will be presented. Multiple imputation will be done using the mice package in R, ten imputations will be derived, and the selected model will then be fit to these datasets, and the results will be compared with the complete case dataset.

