### Out of Hospital Cardiac Arrest & Quality Improvement Registries

The science underpinning the ‘chain of survival’ is unquestionably of critical importance in OHCA care. However, scientific research alone will not be sufficient to improve OHCA outcomes and must be accompanied by a focus on real world implementation and quality improvement
^
24
^. To this end the European Resuscitation Council recommend that ‘health systems should have population-based registries which monitor the incidence, case-mix, treatment and outcomes for cardiac arrest’ and that these data ‘should inform health system planning and responses to cardiac arrest’
^
25
^.

An internationally agreed ‘Utstein’ registry dataset has been devised which facilitates national and international comparison of OHCA
^
26
^. A recent pan European survey reported that six countries (including Ireland) had an OHCA registry with full population coverage, fourteen had partial population coverage and seven countries reported not having an OHCA registry
^
27
^. Comprehensive data on the Irish experience of OHCA is provided by the Irish Out-of-Hospital Cardiac Arrest Registry (OHCAR). OHCAR achieved national coverage using the Utstein dataset in 2012, and by 2020 this contains over 20,000 cases. In terms of the period considered in this study OHCAR does not include OHCA with EMS response but without attempted resuscitation. We anticipate that approximately fifty percent of cases recorded in OHCAR are witnessed (European average 66%), and twenty percent have an initial ‘shockable rhythm’ (European average 20%)
^
6
^. The primary sources of OHCAR data are patient care records and dispatch data from Ireland’s statutory ambulance services. OHCAR has provided invaluable continuous quality improvement data on an annual basis to ambulance services. To date however, no temporal analyses have been conducted to assess the impact of national interventions on survival in Ireland. Nor has the database been interrogated to determine whether international trends in OHCA (including increased bystander CPR and associated survival improvements
^
28–
30
^) are mirrored in the Irish data.

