### Variables and categories of concern

All analysis will be based on the variables shown in
Table 1. Variables 1–19 will be obtained from the OHCAR. Variables 20, 21 and 22 represent component time periods that are a priori considered to be potentially significant in the context of either system level developments or key population health challenges (Covid-19) during the study time period. Variables 20,21 and 22 will be dummy variables created using the ‘Year’ variable. Variables 20 and 21 will be linked dummy variables derived from the same 3-level categorical indicator of period and will be simultaneously included in regression models. We do not expect collinearity of these predictors, as transition and post-transition period correspond to years 2015 and 2016, and 2017 through 2020, respectively. The Covid period dummy variable (variable 22) will be an indicator of 2020 only, and thus should allow us to estimate any shift in survival in the final year of the study data.
Table 1 highlights the independent variables that will be explored for each outcome of interest. Where an original OHCAR variable has multiple potential associated categories, we will collapse these categories to avoid decreased statistical power from analysis of an excessive number of potentially sparse categories. Original and collapsed categories are shown in
Table 1. Season will represent the ‘winter’ healthcare period (October to March) as compared to other as ‘winter’ is a period of increased demand for the Irish healthcare service. The three time categories chosen are adopted based on previous OHCA research
^
44
^. Home (versus other) location was chosen as home represents the most common location for OHCA in Ireland. ‘Year’ (variable 9) will be treated as a continuous variable to conserve degrees of freedom and statistical power.

**Table 1. T1:** Variables for analysis.

Variable Number	Variable	Categories	Collapsed Categories	Outcome of Interest		
				Bystander CPR	Bystander Defibrillation	Survival to Hospital Discharge
**1**	**Airway** ** Management**	**Basic ** **Management**	**None of the listed devices ** **used, OPA/NPA, No advanced** ** airway**			*****

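### Missing discharge survival probably falls mainly on transported patients, but Table 1 has no variable that identifies them, so complete-case analysis and, to a lesser extent, imputation from Table 1 can misestimate survival

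*Protocol article*

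**What the plan says.** Under 'Missing data and sensitivity analysis', the protocol article states: "We anticipate some missing data in both the outcome and predictor variables". It will document the amount of missing data per variable and graph the patterns. Its sensitivity analysis is that "results from complete case analysis and multiple imputation will be presented". On method it adds: "Multiple imputation will be done using the mice package in R, ten imputations will be derived". It does not list the variables in the imputation model.

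Under 'Variables and categories of concern' it states: "All analysis will be based on the variables shown in" Table 1. For survival, Table 1 marks all 22 numbered variables. They include initial rhythm, airway management, shocks, adrenaline doses, amiodarone, mechanical CPR and who witnessed the collapse. None records transport to hospital, death at the scene, return of spontaneous circulation (ROSC) or status at hospital handover.

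On sources, the section on registries says: "The primary sources of OHCAR data are patient care records and dispatch data from Ireland’s statutory ambulance services". The article does not describe how discharge status is obtained. The Discussion leaves linkage to hospital in-patient data to a later project.

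**The concern.** A patient declared dead at the scene has a known value for survival to discharge: no. A patient handed over to a hospital has an outcome that arises later, outside the ambulance record. If discharge status is unknown, the patient was therefore probably transported, and every survivor comes from that group.

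Complete-case analysis would then delete records only from the group that contains the survivors. Imputation from Table 1 would fill these records in from observed patients with similar covariates, who are a mix of scene deaths and transported patients. Missingness may be at random once transport is known, yet not at random given Table 1 alone.

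Aims 3 and 4 are comparisons over time. If the completeness of hospital outcomes changed between the periods before and after the control-centre transition, or in 2020, part of that change would appear as a transition or Covid effect on survival.

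**Working it through.** The article gives no missing-data figure to reproduce, so the check is a range under stated assumptions.

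**Inputs**
- From the article: survival S is 6–7% ("six to seven percent involve survival to hospital discharge"), with 6.5% used as the midpoint. For the size of the data set: "We anticipate approximately 18,000 relevant observations will be available for analysis".
- Assumed: a share t of patients is transported, and a fraction m of them lacks discharge status, at first independently of survival.

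**1. Complete-case survival.** The survivors kept are S(1 − m) and the records kept are 1 − t·m, so complete-case survival = S(1 − m)/(1 − t·m).

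Example with S = 6.5%, t = 30%, m = 10%: 0.065 × 0.90 / (1 − 0.03) = 0.0585/0.97 = 6.03%.

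Over S = 6–7% and t = 30–60%, the ratio of estimated to true survival is:

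| m | ratio |
|---|---|
| 1% | 0.993–0.996 |
| 5% | 0.964–0.979 |
| 10% | 0.928–0.957 |
| 20% | 0.851–0.909 |

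**2. Spurious period odds ratio, missingness in one period only (S = 6.5%, true OR 1).** For t = 30%, m = 10%: (0.0603/0.9397)/(0.065/0.935) = 0.0642/0.0695 = 0.92.

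| m | t = 30% | t = 50% |
|---|---|---|
| 5% | 0.96 | 0.97 |
| 10% | 0.92 | 0.94 |
| 20% | 0.84 | 0.88 |

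At m = 1% and t = 30%, survival is 6.45% and the OR is (0.06454/0.93546)/(0.065/0.935) = 0.99.

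**3. Missingness in both periods (t = 40%, true OR 1, later versus earlier).** Equal missingness gives 1.00. With 10% before and 2% after it is 1.06; with 2% and 10%, 0.95; with 20% and 5%, 1.12.

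**4. Opposite direction.** If only transported deaths lack the outcome, at rate m, estimated survival = S/(1 − (t − S)m). With t = 40%, 6.5% becomes 0.065/(1 − 0.335 × 0.05) = 6.61% at m = 5%, and 6.73% at m = 10%.

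**5. What imputation does.** A simulation used 18,000 patients, 20 replicates, 10 imputations, about 41% transported, and missingness unrelated to survival among those transported. The covariates were shockable rhythm (20%), witnessed collapse (50%) and period.

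| m | true | complete case | imputed without transport | imputed with transport |
|---|---|---|---|---|
| 5% | 7.13% | 6.92% | 6.98% | 7.14% |
| 10% | 7.18% | 6.72% | 6.85% | 7.16% |
| 20% | 7.17% | 6.24% | 6.50% | 7.17% |

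Imputation without transport recovered (6.85 − 6.72)/(7.18 − 6.72) = 28% of the gap at m = 10%. The treatment variables in Table 1, which the simulation did not include, might recover more. The odds ratio for shockable rhythm moved little: 14.3 to 14.6 at m = 10%, and 14.6 to 15.3 at m = 20%, with or without imputation.

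**6. The fix on the example from step 1.** Of 2,000 patients, 600 are transported, 130 survive and 60 transported outcomes are missing, which leaves 117 survivors among 540. Imputing within the transported gives 117 + 60 × 117/540 = 130, or 6.5%. The bounds are 117/2,000 = 5.85% with all missing dead and 177/2,000 = 8.85% with all alive.

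**The case against.** The premise is not in the article. It does not say who lacks discharge status, how many do, or whether the outcome with missing values is survival rather than one of the two bystander outcomes. Ambulance and dispatch records are called primary sources, not the only ones, and the ethics section shows some contact with hospitals. Missing discharge status could be close to zero, and then nothing here matters. This objection stands as a limit on the size. It does not remove the structural point, because the article itself expects missing outcomes.

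It can also be said that a fuller analysis plan may name auxiliary variables, and that the Table 1 sentence was written with model predictors in mind. That is possible. As written, however, the sentence covers all analysis, and Table 1 offers only partial proxies for transport.

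Several stronger readings are tempting, and the material does not support them:
- That the methods treat missing patients as if they had died at the scene. They treat them like observed patients, and imputation from Table 1 matches on covariates.
- That survival must be biased downward. Step 4 shows the reverse is possible.
- That the two planned analyses would agree and so falsely reassure. In the simulation they differ, and imputation moves towards the truth, although most of the bias remains.
- That the transition and Covid odds ratios are biased in any case. With equal missingness across periods they are not, and the article gives no evidence of a difference by period.

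**Conclusion.** The point holds in a conditional form. The plan expects missing outcomes and restricts analysis to a variable list that cannot tell scene deaths from transported patients. If missing discharge status falls mainly on transported patients, which is likely but inferred, complete-case survival is biased, and imputation from Table 1 corrects only part of this. The direction depends on whether, among those transported, missingness is related to survival.

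The relative error in survival is under 1% at 1% missing, about 4–7% at 10% and about 9–15% at 20%, for 30–60% transported and missingness unrelated to survival. For aims 3 and 4 the error arises only from a difference in missingness between periods; the OR of about 0.92 is an illustration with missingness in one period only and no recovery from covariates. The transport and missingness fractions are assumptions. A reader might infer that the imputed analysis must become the primary one. That is a preference and does not follow from this check.

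**What to change.** - Request from the registry whether each patient was transported or died at the scene and, if held, ROSC at hospital handover.
- Amend the Table 1 restriction so that these fields may enter the imputation model as auxiliary variables only, not as predictors of survival. Set scene deaths to non-survival and impute discharge status only among transported patients.
- Tabulate missing discharge status by year among transported patients.
- If it is not negligible, add a sensitivity analysis for the transition and Covid effects with missing outcomes set to all survived and to all died. Imputation with transport status still assumes that missingness among the transported is unrelated to survival given the covariates, and the bounds show how much rests on this. They can be wide: 5.85% to 8.85% in the worked example.

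The cost is one or two extra fields in the anonymised extract, assumed to be available, and a little more analysis work. No new data collection is needed if the fields are held.
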